### Adherence to interventions

Participants on the intervention arm will be given monthly study visits in which the adherence software shall be read to determine information on use of the medicine cap and box. Based on the information displayed, study personnel provide tailored adherence counselling to the participants. For participants below the age of 18 and under guardianship, their caretakers will be included in the adherence counseling sessions.

### Determination of TB treatment outcomes

At the end of therapy treatment (9 months for participants that qualify for shorter MDR-TB/RR-TB treatment regimen and 18 months for those selected for the longer MDR-TB/RR-TB treatment regimen), clinical and laboratory information is routinely compiled by each MDR-TB centre and forwarded to the National TB Program (NTP) review committee for discussion on consensus on treatment outcome based on a specified criterion (Table 2). TB treatment outcomes for this study will be as determined by the review committee.

**Table 2 Tab2:** Description of MDR-TB treatment outcomes

**Outcome**	**Definition**
Time to culture conversion	Time from initiation of treatment to the time point where the patient has two consecutive negative cultures
Cured	1. A patient who has culture converted and 2. Received treatment for a total duration of 9–11 months and 3. Has at least 3 consecutive negative TB cultures at least 30 days apart and 4. No evidence of clinical deterioration
Treatment completed (success)	1. A patient who has culture converted and 2. Received treatment for a total duration of 9–11 months and 3. Has less than 3 consecutive negative TB cultures at least 30 days apart and 4. No evidence of clinical deterioration
Loss to follow-up	A patient with treatment interrupted for 2 consecutive months and more
Treatment failure	1. A patient who failed to culture convert by month 5 (shorter regimen) or month 6 (longer regimen) or 2. In the initial 6 months of treatment more than 2 of 5 cultures are positive or 3. Treatment stopped due to adverse events 4. Permanent discontinuation of two Group A drugs (BDQ, LZD, or LFX) in the first 6 months of the modified shorter regimen or 5. More than 2 new drugs added because of poor clinical response or 6. Panel decision to terminate any further DR-TB treatment
Died	A patient who died for any reason during treatment

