#### Diagnosis and management of MDR-TB

Diagnosis of MDR-TB is based on Gene Xpert® testing of sputum for identification of resistance to rifampicin (RR-TB) followed by culture and drug susceptibility testing (DST) for phenotypic characterization; however, treatment is started prior to the receipt of culture and sensitivity results due to long turnaround time of 10–16 weeks. Treatment options for MDR-TB/RR-TB currently include:Category 1—A bedaquiline-based injection-shorter treatment regimen (STR) (9 to 12 months) reserved for MDR-TB/RR-TB patients who have not been previously treated with second-line drugs and in whom resistance to fluoroquinolones and second-line injectable agents has been excluded. Drug options for shorter treatment regimen include an intensive phase of 4 months (extended to 6 months in case of delayed sputum smear conversion) containing high-dose gatifloxacin or moxifloxacin, kanamycin, prothionamide, clofazimine, high-dose isoniazid, pyrazinamide, and ethambutol followed by a continuation phase of 5 months containing gatifloxacin or moxifloxacin, clofazimine, ethambutol and pyrazinamide [12].Category 2—The longer treatment regimens (18 to 20 months) based on core backbone agents but individualized depending on age, fluoroquinolone resistance, and site of disease.

According to standard of care, patients with MDR-TB are managed as in-patients at central MDR treatment facilities (which include Mulago and Lira hospitals) in the intensive phase of treatment after which they are discharged and required to report to the central MDR treatment facility monthly for review and drug refills. Following discharge, during the continuation phase, patients are required to report daily to the nearest private or public facility registered under DOT programme [13]. Monthly reviews during routine care include safety laboratory investigations including a full blood count, liver and renal function tests, sputum culture, DST and adherence counseling.

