#### Eligibility criteria

We shall enrol consented patients with newly diagnosed pulmonary MDR-TB and RR-TB patients aged ≥8 years, initiated on oral MDR-TB therapy (category 1 or 2). Patients with any condition that inhibits the use of the MEMS device, e.g. dexterity or debilitating arthritis, will be excluded from participation.

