## Laboratory assessments

Blood sampling to measure the concentrations of bedaquiline and linezolid will be conducted on months 2, 8 and 11 of treatment. Drug intake on the days for blood sampling will be performed by DOT and blood samples taken off prior to drug intake and 1-h post-drug intake. The blood samples will be placed in cooler boxes and transported to the laboratory on dry ice for samples from Lira Hospital and in a cooler box for samples from Mulago Hospital, processed and stored at −4 to −80 °C. Pharmacokinetic analysis will be performed at the Infectious Diseases Institution (IDI) translation laboratory. Quantification of the drug concentrations will be performed in batches using validated high-performance liquid chromatography (HPLC) and mass spectrometry at the Translation Laboratory of the Infectious Diseases Institute, Makerere University using MS.

Sputum smears and cultures will be performed as part of routine care and testing conducted at the government reference laboratory.

The study follow-up duration will be 24 months to cater for patients on both short- and long-term oral MDR-TB therapy. Treatment duration will be approximately 9 to 18 months: 9 months for participants that qualify for shorter MDR-TB/RR-TB treatment regimen and 18 months for those selected for the longer MDR-TB/RR-TB treatment regimen.

To ensure data quality, study information is captured with an e-questionnaire in Redcap that has been designed to send real-time notifications for inputted variables that may be out of range. The tool also does not accept for the person collecting data (medical officer and or study nurse) to verify the tool, but is redirected to the study coordinator and Data Manager to do the final verification for correct and missing data. In addition, the entire study team was trained afore on the use of the study Redcap tool and on other study-related standard operating procedure manuals including the collection of blood specimens for continued reference. In the event of a protocol violation, retraining on study protocol and procedures will be conducted.

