#### Secondary outcomes

To assess correlation of specific MDR-TB drug serum concentrations with observed adherence, bedaquiline and linezolid pre-dose concentrations (C_trough_) will be used. To cater for those who may be adherent but have low bedaquiline or linezolid concentrations, we will use of cut-off value of bedaquiline C_trough_ from previous studies, below which a participant will be classified as non-adherence. Linezolid will be used to assess more recent adherence than bedaquiline.

We will compare time to sputum culture conversion in the intervention and control arm using time to event analysis. We shall also use chi-square testing to compare treatment success rates in the intervention and control arms. Treatment success will be evaluated using a composite outcome that includes TB cure (for microbiologically diagnosed patients) and TB treatment completion (for clinically diagnosed TB). We will undertake per-protocol and intention to treat analyses to compare TB cure rates in the two study arms. We will determine the proportions of patients retained in care of retention in care at 2 and 6 months in the two study arms using chi-square tests. Study outcomes by randomization arm will be compared using a generalized estimating equations (GEE) model using repeated measures with identity link, exchangeable correlation structure and robust variance estimates. Adjusted coefficients along with their corresponding 95% CIs will be generated. Statistical significance will be set at the *P* < .05 level and statistical analyses performed using Stata version 14 (StataCorp, College Station, TX, USA).

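### Table 2's 9–11-month duration criterion for both success outcomes does not fit the eligible 18–20-month regimen, and the protocol defines treatment success in two conflicting ways

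*Protocol article*

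**What the plan says.** **Outcome definitions.** In Determination of TB treatment outcomes, Table 2 lists "Received treatment for a total duration of 9–11 months" as a required element of both Cured and Treatment completed (success). The two rows differ in the number of consecutive negative cultures: at least 3 for cure, fewer than 3 for completion. Both also require culture conversion and no clinical deterioration. The text above the table says that a national review committee assigns the outcome by consensus on a specified criterion, and cites Table 2 for it.

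**Who is enrolled.** Eligibility criteria admits patients "initiated on oral MDR-TB therapy (category 1 or 2"). Diagnosis and management of MDR-TB describes category 2 as "The longer treatment regimens (18 to 20 months) based on core backbone agents" and category 1 as lasting "9 to 12 months) reserved for MDR-TB/RR-TB patients" who meet further conditions.

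**When outcomes are judged.** Determination of TB treatment outcomes sets assessment at the end of therapy, including "18 months for those selected for the longer MDR-TB/RR-TB treatment regimen". Laboratory assessments adds: "The study follow-up duration will be 24 months to cater for patients on both short- and long-term oral MDR-TB therapy".

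**The success composite.** Secondary outcomes defines treatment success as "TB cure (for microbiologically diagnosed patients) and TB treatment completion (for clinically diagnosed TB"), to be compared between arms by chi-square test.

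**The concern.** There are two separate contradictions.

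First, the duration condition in the two success rows matches only the shorter regimen, although the trial enrols, follows and assesses patients on both. Taken at its word, the table gives no outcome to a longer-regimen patient who does well.

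Second, the protocol sorts successes in two incompatible ways. Table 2 separates cure from completion by culture count and calls completion a success. Secondary outcomes separates them by how the disease was diagnosed. The same patient can be a success under one rule and not under the other.

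Treatment outcome by arm is a listed secondary outcome, and comparing it is a stated secondary objective. If the definition is not settled in advance, the success rate depends on which text is followed. The choice could then fall to people who know the allocation, since the trial is open-label.

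**Working it through.** The plan gives no computed figure for this endpoint, so there is none to reproduce. The check is to compare the texts and then illustrate the effect.

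**1. Duration windows.**
- Success rows of Table 2: 9–11 months.
- Longer regimen: 18–20 months (Diagnosis and management of MDR-TB); 18 months (Determination of TB treatment outcomes; Laboratory assessments).
- Shorter regimen: 9–12 months (Diagnosis and management of MDR-TB); 9 months (the other two sections).

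The longer regimen starts 18 − 11 = 7 months after the window closes, so there is no overlap. A 12-month shorter course misses it by 12 − 11 = 1 month. The window does match the shorter regimen's phases: 4 + 5 = 9 months, or 6 + 5 = 11 months with the extended intensive phase.

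**2. Is Table 2 meant only for the shorter regimen?** No. Its failure row sets a culture-conversion limit of month 5 for the shorter regimen and month 6 for the longer. The table covers both regimens, but the success rows do not.

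**3. Where does a successful longer-regimen patient go?** Someone who converts, finishes 18 months and stays well is outside both success rows on duration. That patient also does not meet the failure, loss-to-follow-up or death rows. No final outcome row remains.

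**4. Completion under the two rules.** Consider a patient with a positive sputum resistance test who converts, finishes a 9-month course, has two consecutive negative cultures and does not deteriorate.
- Table 2: Treatment completed, labelled success.
- Secondary outcomes: not cured, and not clinically diagnosed, so not a success.

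Diagnosis and management of MDR-TB bases diagnosis on a sputum molecular test followed by culture and susceptibility testing. Most or all completers would therefore be classified differently by the two rules. The document gives no split of cure and completion, so this effect cannot be sized.

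**5. Worst-case size of the duration problem.** Let f be the share on the longer regimen, which is not given and is assumed here. Take 77.9% (Sample size) as true success in both regimens, and suppose that no longer-regimen patient is recorded as a success. Then measured success = 77.9% × (1 − f), and the number affected = 164 × f.

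| Assumed f | Highest attainable success | Expected success | Participants affected |
|---|---|---|---|
| 5% | 95% | 74.0% | about 8 |
| 10% | 90% | 70.1% | about 16 |
| 20% | 80% | 62.3% | about 33 |
| 30% | 70% | 54.5% | about 49 |
| 50% | 50% | 39.0% | 82 |

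**6. Dilution.** With the same f in both arms and the same true difference d in both regimens, the measured difference is d × (1 − f). At f = 20%, a true 10-point difference would appear as 10 × 0.80 = 8 points.

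**The case against.** **The committee decides.** Outcomes are those assigned by the review committee, and the same section expects 18-month outcomes for longer-regimen patients. A reader might infer from Table 2 that these patients can never count as successes. The document does not show that they will be recorded that way; the committee may well apply a regimen-specific rule. This objection limits the size but does not remove the contradiction, because the only criterion cited for the committee is Table 2. If it uses another, the published definition is wrong and needs the same correction.

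**Clinically diagnosed patients.** A reader might also infer that completion is reserved for a type of patient the trial does not enrol. Eligibility criteria neither excludes clinical diagnosis nor states a test requirement, so that goes beyond the text. The conflict between the two success rules stands without it.

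**Imbalance between arms.** Randomization is stratified by age group and gender, not regimen. A 10-point difference in f between arms would, under the literal rule, shift measured success by 0.10 × 77.9 = 7.8 points. It is tempting to call this a false treatment effect. If regimen is set at baseline, however, its expected share is equal in both arms, and chance imbalance is sampling variation that the chi-square test already allows for. With 82 per arm, the SD of the imbalance is √(2f(1 − f)/82): 6.2 points at f = 20% and 7.7 at f = 40%. An imbalance of 10 points or more in either direction then has probability of about 11% to 19% (normal approximation). This is noise, not bias.

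**Does the endpoint merely measure regimen length?** No. Culture results and clinical course still decide the outcome for shorter-regimen patients.

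**Condensed article.** That would excuse an omission. These are stated definitions that conflict with other stated text.

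**Conclusion.** The point holds as two contradictions to reconcile. The duration criterion in both success rows of Table 2 does not fit an eligible regimen, nor the upper end of the shorter one. Treatment success is also defined differently in Table 2 and in Secondary outcomes.

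The consequence is a mis-measured secondary endpoint, with success understated and any true difference between arms diluted. Systematic bias between arms is not shown, and the primary adherence comparison does not use these definitions.

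The fall from 77.9% to between 74.0% and 39.0% is a worst case. It rests on an assumed 5% to 50% share on the longer regimen, on equal true success in the two regimens, and on the committee applying Table 2 literally. If the committee already uses a regimen-specific rule, the numerical effect disappears, but the published criterion still differs from the one in use. The point should be corrected, at the weight of a secondary endpoint.

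**What to change.** 1. Reconcile Diagnosis and management of MDR-TB, Determination of TB treatment outcomes (with Table 2), Laboratory assessments and Secondary outcomes. The duration criterion in the two success rows should be specific to the participant's regimen and match what the review committee applies. This review takes no view on which duration is right.
2. Define treatment success once, as cured or treatment completed per Table 2, for all participants, and delete the split by microbiological or clinical diagnosis.
3. Optionally, adjust the comparison for regimen category, using only the category assigned at baseline. Susceptibility results can take 10–16 weeks, so a category settled later may be a post-randomization variable. Once the definition covers both regimens, this is a matter of preference.

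The cost is a wording amendment and confirmation from the committee of the criterion it uses. The treatment dates, culture results and outcomes needed are already compiled in routine care, so no new data are required. The change should be made before outcomes are compared by arm.

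### Table 2 does not require cultures to stay negative and has no reversion criterion, so a clinically stable shorter-regimen patient who turns culture-positive after month 6 can be classed as cured

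*Protocol article*

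**What the plan says.** All the definitions are in Table 2, under Determination of TB treatment outcomes.

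- **Conversion** is dated to "the time point where the patient has two consecutive negative cultures". Nothing revokes it later.
- **Cured** needs conversion, "Received treatment for a total duration of 9–11 months", "Has at least 3 consecutive negative TB cultures at least 30 days apart" and "No evidence of clinical deterioration".
- **Treatment completed (success)** has the same items except the culture one, which becomes "Has less than 3 consecutive negative TB cultures at least 30 days apart".
- **Treatment failure** has two culture-based items. One is non-conversion by month 5 (shorter regimen) or month 6 (longer regimen). The other is "In the initial 6 months of treatment more than 2 of 5 cultures are positive". The remaining items are stopping for adverse events, permanently dropping two Group A drugs in the first six months, adding more than two drugs for poor clinical response, and a panel decision to end treatment.

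The same section says that the national programme's review committee reaches the outcome by consensus on these criteria, and that the trial uses the committee's outcome. The Secondary outcomes section says: "We will undertake per-protocol and intention to treat analyses to compare TB cure rates in the two study arms". It also plans a chi-square comparison of treatment success, a composite of cure (for microbiologically diagnosed patients) and completion (for clinically diagnosed TB).

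**The concern.** The two success categories look back to a past run of negatives and ignore what the cultures show at the end of treatment. For Treatment completed, an interrupting positive culture can even be what keeps the run below three and so places the patient there. No culture-based failure item looks beyond month 6.

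This matters for this trial in particular. The section on diagnosis and management of MDR-TB describes inpatient care in the intensive phase, followed by daily facility DOT in the continuation phase. If unsupervised dosing does bacteriological harm after discharge, late reversion is one form it could take. An outcome that can record such patients as cured is poorly placed to show a difference between arms in that harm.

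**Working it through.** There is no stated figure to reproduce. The check applies the Table 2 rules to culture records.

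**Inputs.** Cultures are monthly, as the routine monthly review in the diagnosis and management section includes sputum culture. The course is 9 months. Assumptions: no clinical deterioration, no drugs added, no drug or treatment stopped early, no panel decision to terminate.

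**Rules coded.**
- Conversion month = the second of two consecutive negatives.
- Failure = no conversion by month 5, or more than 2 early positives.
- Otherwise, Cured = longest negative run of 3 or more, and Completed = a shorter run.

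**Example A:** positive month 1, negative months 2–6, positive months 7–9.
- Conversion is at month 3, so the month-5 failure item is not met.
- There is 1 positive in the first six months, which is not more than 2.
- The longest negative run is 5, which is at least 3.
- Class: Cured, with the last three cultures positive.

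**Example B:** positive month 1, negative months 2–3, positive month 4, negative months 5–6, positive months 7–9.
- Conversion is at month 3.
- There are 2 positives in the first six months, which is not more than 2.
- The longest negative run is 2, which is below 3.
- Class: Treatment completed (success), again with the last three cultures positive.

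**Enumeration.** There are 2^9 = 512 possible nine-month records. Of these, 38 convert by month 5 and are positive at all of months 7–9. The result depends on which cultures the 2-of-5 item refers to:

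| Early positives counted over | Cured | Completed | Failure | Total |
|---|---|---|---|---|
| months 1–5 | 19 | 11 | 8 | 38 |
| months 1–6 | 16 | 5 | 17 | 38 |

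So 30 (19 + 11) or 21 (16 + 5) of the 38 are classed as success under Table 2. All the failures arise from early positives, none from the reversion. These are counts of rule paths. They are not probabilities and say nothing about how many patients revert.

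**Longer regimen.** Its course is 18 months, outside 9–11, so no 18-month record can be Cured or Completed. The effect described here does not arise in those patients.

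**Illustration of scale, on assumption only.** The documents give no reversion rate. If a share r of patients classed as success had in fact reverted, success would be overstated by r × the success rate. With the programme's 77.9% as a stand-in:
- r = 2%: 0.02 × 77.9 = 1.6 points
- r = 5%: 0.05 × 77.9 = 3.9 points
- r = 10%: 0.10 × 77.9 = 7.8 points

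The 77.9% is a past national figure and not this trial's, and every r is assumed.

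**The case against.** The strongest reply is that Table 2 guides a panel and is not a scoring algorithm. The committee sees the compiled record at the end of therapy and could read the three-negatives item as status at that point. It could treat late positive cultures as clinical deterioration, which the article does not define, or it could use the added-drug or termination items. This stands to the extent that nobody can say every late reverter will be recorded as a success. It does not remove the defect. The committee's stated criterion is this table, and a clinically stable patient who finishes the planned course triggers none of those items. If the committee has to depart from the table to avoid calling a culture-positive patient cured, the outcome rests on an unwritten rule.

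A second reply concerns the composite. The Secondary outcomes section ties completion to clinically diagnosed TB, while diagnosis in this trial is by GeneXpert followed by culture. On that wording a patient such as Example B would not enter the composite at all. Table 2, which labels completion as success without that limit, points the other way. This stands: the effect through completion is uncertain until the two sections are reconciled.

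Third, Study outcomes lists sputum conversion at 2, 8 and 11 months by arm. If that is assessed as status at each visit, the later time points could reveal some reversions. So it would be too much to say that the trial cannot see them.

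Finally, a journal table may condense fuller programme criteria. But the article states these definitions as the criteria, so the point concerns stated text and not an omitted detail.

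**Conclusion.** The point holds as a defect of definition in a secondary outcome. As written, a clinically stable shorter-regimen patient who reverts after month 6 can be classed as Cured, and some as Treatment completed (success), unless the committee departs from Table 2 or uses the added-drug or termination items. The cure comparison is affected in both its intention-to-treat and per-protocol forms. The success composite is affected only as far as completion counts there.

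A reader might infer that every patient who reverts after month 6 is scored as a success, or that a known number of percentage points is lost. The documents support neither. The first fails for patients with clinical deterioration, for those caught by another failure item and for the 18-month regimen. The second needs a reversion rate, which the documents do not give. The primary adherence comparison is untouched.

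**What to change.** For the trial's own cure and success comparisons, state that a patient with culture reversion after conversion and before the end of treatment is not counted as a success. Two consecutive positive cultures would mirror the two-negative conversion rule. That threshold is only an example and should be agreed with the national programme. Derive the variable from the routine monthly cultures, and report the committee-assigned outcome alongside it. In the same edit, reconcile Table 2 with the Secondary outcomes section on whether completion counts as success for microbiologically diagnosed patients. This concerns outcome scoring for analysis only and changes no treatment decision.

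The cost is a few lines of text and one derived variable, with no new cultures. The downside is that success may be slightly lower and may differ from the programme's label for a few patients.
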